### Interventions

CRT and SAT are both delivered in 10 bi-weekly sessions directly preceding TAU. As AN patients will need to be closely monitored and given nutritional advice throughout the study, the relevant treatment components will be part of the first treatment phase in this group. Other components of (psychological) treatment will not be offered until CRT/SAT has been completed.

### Cognitive remediation therapy

In this trial, CRT is based on the Dutch translation of the original manual by Kate Tchanturia [119] for both patient groups. Comprising 10 twice weekly 45-min sessions, CRT is delivered by psychologists, clinical nurses, and psychology students (at the MSc level), all having been trained by experienced CRT therapists (UD, BvP, LS, DC) who themselves were trained by [name], expert on CRT for eating and weight disorders. Using a range of cognitive lab-based exercises, CRT aims at improving patients’ set-shifting, cognitive flexibility, global information processing skills, and at reducing perfectionism. Table 2 lists the within-session exercises used in the RCT.

**Table 2 Tab2:** CRT exercises

Central coherence tasks	Maps Summarize a letter Hidden words Word-search task Embedded word task
Set shifting tasks	Card Stack Visual illusions Stroop material Switching attention task Switching Time Zones Alphabet task
Perfectionism tasks	Estimation task
Strategy tasks	How to plant a sunflower Complex figure task

For a more detailed description of the exercises, see Tchanturia et al. [119]. With respect to carrying out the exercises, awareness of dysfunctional thinking styles is enhanced. Patients are encouraged to find out how these thinking styles affect their daily lives, and from session 2 onward, homework assignments are given comprising behavioural exercises that are closely linked to real-life skills and tasks to thus stimulate patients to practice more flexible behaviours in their everyday lives.

### Specialized Attention Therapy (SAT)

SAT has been designed as the control intervention specifically for this trial. SAT is delivered by the same health professionals delivering CRT. The SAT session structure (10 twice weekly, 45-min sessions and homework assignment) is the same as in CRT. However, during SAT, cognitive flexibility, central coherence, global information processing skills, awareness of thinking styles, and reducing perfectionism are not addressed. Instead, after each task patients are asked their opinion on whether they (dis)liked the task. As a treatment rationale, patients are explained that SAT aims at helping them to focus on positive experiences by means of tasks and exercises, where each session–again in line with CRT–comprises different exercises. For an overview of the exercises practiced in SAT, see Table 3; for a more detailed description of the exercises, the SAT treatment manual is available upon request [120].

**Table 3 Tab3:** SAT exercises

Motor tasks	Djenga Mikado Leaning Tower of Pisa Operation Game
Luck tasks	Game of the Goose Ludo Snakes and ladders
Collaboration task	Drawing a picture together
Picture tasks	Spot the differences Viewing a picture
Verbal tasks	Last letter-first letter Incomplete sentences task Poems
Additional tasks	Listening to music Analogies Categories

From session 2 onward, patients are encouraged to engage in similar activities at home that they enjoy.

### Treatment as usual

After completion of either CRT or SAT, patients receive TAU. The content of TAU comprises all the essential elements recommended in the Dutch guidelines on eating disorders and OCD, which are closely related to the international guidelines [121, 122].

TAU for patients with AN consists of normalization of eating behaviours (weight gain), discussion of daily problems, goals, psycho-education, and for a subgroup psychomotor therapy, art therapy, social skills training, family-therapy or cognitive behavioural therapy. Psychiatric- and/or medical consultation and pharmacotherapy is given where needed.

TAU for OCD patients comprises CBT delivered in 20 to 30 weekly or twice weekly 45–90 min sessions in which exposure with response prevention forms a key element, consistent with the multidisciplinary guidelines for anxiety disorders (OCD chapter) [121]. In line with the literature [123, 124], the OCD protocol is flexible, i.e., patient-tailored with regard to the time spent on each component, accounting for differences in session and treatment duration. The therapy encompasses a) psychoeducation, b) cognitive therapy, c) exposure in vivo with response prevention, d) psychiatric consultation, and, in case of severe symptoms, pharmacotherapy with SSRIs, venlafaxine, clomipramine and/or atypical antipsychotics. The protocol allows for one or two sessions in which the principles of CBT are explained and one or two sessions in which an inventory is made of all anxiety/tension-provoking situations that give rise to compulsions and a construction of a list of compulsion triggers. All patients receive in- and between session exposure to anxiety-provoking thoughts and situations, coupled with prolonged response prevention tailored to their individual symptoms.

### Treatment fidelity

To ensure treatment fidelity for CRT and SAT, the best practices and recommendations from the NIH Behaviour Change Consortium [125] are followed. The number, duration, and frequency of sessions, as well as patient-therapist contact times are kept the same for CRT and SAT. All patient-therapist contacts are formally scheduled to ensure fixed durations. All treatment sessions are audio- or videotaped and an external checker not involved in the trial rates treatment fidelity in a random selection of 10% of the recorded sessions. To evaluate, guide, and approve interventions, and to constrain ‘therapist drift’, all therapists are supervised by expert professionals, and have at least monthly intervision-sessions. After every session, the therapist completes a brief questionnaire to record treatment stage and components delivered. Deviations from the protocol are reported to the supervisor.

### Analyses

Baseline differences between the CRT and SAT (control) groups and between the participating centres are investigated using χ^2^ tests for categorical variables and ANOVAs for continuous variables. Additional exploratory analyses are conducted separately for AN and OCD.

The data for the primary AN and OCD outcome indices are analysed using linear mixed models (LMM) with the baseline value as a covariate. The mixed models analysing the general efficacy of CRT include a random term for the intercept and fixed terms for condition, time contrasts (T0–T1, T0–T2, T0–T3, T1–T2, T1–T3), and the interactions between condition and time contrasts.

In order to investigate moderators of short- and long-term treatment response, time contrasts are created (T0–T1, T0–T2, T0–T3, T1–T2, T1–T3) by means of dummy coding. Potential continuous moderator variables are standardized. Interactions between condition and the potential moderators are entered into the equation. All analyses on therapy effect modificators are of an exploratory nature. The moderator and mediator analyses are calculated with 5000 bootstraps [126].

To assess the cost-effectiveness of CRT + TAU versus SAT + TAU for ED and OCD, all relevant costs and effects are taken into account. Disease progression is described in terms of transitions between ‘states’, where a patient’s ‘state’ can shift in either direction or remain constant. Estimations of state-transition rates are based on the data from the ongoing trial and the literature, which modelling approach serves to help us assess future scenarios. Costs and effects are calculated in accordance with recommendations in the Dutch guideline for economic evaluation of health care. As a primary assessment we apply a costs-utility analysis that yields a cost per quality-adjusted life years (QALY) outcome, a common cost-effectiveness measure that allows comparison with economic evaluations of other diseases and interventions. The uncertainty estimations are computed using bootstrapping and the results expressed in an acceptability curve. If no intervention is effective, a cost-minimization calculation is performed.

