### Participants

Patients aged between 18 and 60 years are recruited from four Dutch tertiary clinics specialized in the treatment of anxiety and eating disorders. Patients diagnosed with AN (both restrictive and binge/purge subtype) are recruited from Altrecht Eating Disorders Rintveld, Zeist, and Rivierduinen Eating Disorders Ursula, Leiden, and patients with OCD from Altrecht Academic Anxiety Centre, Utrecht, and Overwaal Centre for Anxiety Disorders, Nijmegen. Most of the patients referred to these centres suffer from moderate to severe AN or OCD.

Eligible are patients whose AN (or eating disorder not otherwise specified, clinically referred to as AN) or OCD diagnosis is consistent with the Diagnostic and Statistical Manual of Mental Disorders, fourth edition text revision (DSM-IV-TR ).

The criteria for exclusion are: severe neurological illness (including a history of seizures, stroke, or Parkinson’s disease), severe comorbid psychiatric disorder (clinical significant major depressive disorder, current acute phase of bipolar disorder, current psychosis, substance dependence/abuse), intellectual impairment, defined as an IQ < 80, estimated with the Dutch Adult Reading Test (DART) [61], which is a Dutch version of the National Adult Reading Test (NART) [62], and inability to adequately speak or read Dutch. Current use of antidepressants and antipsychotics is allowed provided that dosages are kept constant during the experimental part of the study. Since benzodiazepines can dampen the effect of cognitive treatments [63], their use is restricted to a daily maximum dose (up to 20 mg for temazepam or an equivalent dose) taken as a sleep medication. On request, patients can withdraw their participation at any time.

Inclusion and exclusion criteria are verified with the aid of the structured clinical interview for DSM-IV-TR axis I disorders (SCID-I [64]), while for OCD patients to be enrolled, a Yale-Brown Obsessive-Compulsive Severity Scale score ≥16 is required [65, 66]. In all patients comorbidity with either OCD or AN is allowed.

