### Outcome measures

The primary outcome measures are: 1) disease-specific psychopathology: Eating Disorder Examination Questionnaire (EDE-Q) [70] for AN severity; Yale-Brown Obsessive Compulsive Scale (Y-BOCS) [65, 66] for OCD severity.

The Eating Disorder Examination Questionnaire (EDE-Q) [70, 71] is the self-report version of the Eating Disorder Examination (EDE) [72], a semi-structured interview to evaluate ED psychopathology. The EDE-Q assesses attitudinal and behavioural aspects of EDs over a 28-day period. It has four subscales assessing concerns about shape, weight and eating, and restraint. The EDE-Q consists of subscale scores and a total scale score. The EDE-Q has excellent internal consistency (Cronbach α 0.78-0.93). The subscales have also excellent test-retest reliability over a 2-week period (Pearson r ranging from 0.81 to 0.94) [73].

The 10-item Yale-Brown Obsessive-Compulsive Severity Scale (Y-BOCS) [74] is a clinician-rated, semi-structured interview-based scale that is broadly used to assess obsessive-compulsive symptom severity. The scale has two parts, each with five questions, with each subscale assessing five aspects of OCD pathology: 1) time consumed, 2) degree of interference, 3) distress, 4) resistance, and 5) perceived control. The first subscale gives an obsession score (maximum: 20), the second a compulsion score (maximum: 20), and together yield a total score (maximum: 40). It has a strong internal consistency (Cronbach α .88-.91), inter-rater reliability (r 0.82–0.98), and test-retest reliability in clinical and nonclinical samples were excellent.

The secondary outcome measures are: 1) disease-specific psychopathology: Obsessive-Compulsive Inventory-Revised (OCI-R) [75], 2) quality of life and daily functioning: EuroQol (EQ-5D) [76], Eating Disorder Quality of life questionnaire (ED-QoL) [77], Obsessive Compulsive Disorder Quality of life questionnaire (OCD-QoL) [78], and Work and Social Adjustment Scale (WSAS) [79], 3) cost-effectiveness (direct and indirect health-related costs as evaluated by means of patients’ self-reported QoL ratings and medical and societal burden: Trimbos/iMTA Questionnaire for Costs associated with Psychiatric illness (TiC-P) [80], 4) general anxiety: Beck Anxiety Inventory (BAI) [81], and 5) Depression: Beck Depression Inventory, second revision (BDI-II) [82].

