### Power and sample-size calculation

In accordance with Cohen [117], we calculated the sample sizes needed to detect treatment-specific differences: CRT + TAU vs. SAT + TAU, for which we used software by G-power [118].

We based effect-size calculations on Dingemans’ first RCT [57] comparing CRT + TAU with TAU alone for eating disorders in which they obtained large effect sizes for reduction in eating disorder pathology (Cohen’s d: 0.99). Given the control condition in this study we take into account a smaller effect-size. In the case of two-tailed MANOVAs, repeated measures and four within-between interactions (2 groups: AN and OCD), two conditions (CRT + TAU vs. SAT + TAU), three measurements (baseline, and 2, and 6 months after baseline), with alpha = 0.05, a sample size of 113 patients is needed to have a power of at least 0.80 to detect an effect size f(V) of 0.25. Although the dropout rate in the previous CRT studies of Dingemans was low (*n* = 7 out of 82 patients), we have opted to include an additional 15 patients to compensate for attrition, totalling 128 patients in total (64 CRT + TAU and 64 SAT + TAU).

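### The sample size is for one model with AN and OCD together, but the primary outcome is a different scale in each disorder and the listed efficacy model has neither a disorder term nor a common scale

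*Protocol article*

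**What the plan says.** All of this is in the Methods/design part of the protocol article.

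- **Outcome measures.** The primary severity measure depends on the diagnosis: "Eating Disorder Examination Questionnaire (EDE-Q) [70] for AN severity; Yale-Brown Obsessive Compulsive Scale (Y-BOCS) [65, 66] for OCD severity". For the Y-BOCS, the two subscales "together yield a total score (maximum: 40" points. The EDE-Q is described only by its structure ("The EDE-Q consists of subscale scores and a total scale score"), without a range. No SD is given for either scale.
- **Power and sample-size calculation.** One calculation covers both diagnoses: AN and OCD as groups, two conditions, three measurements, alpha 0.05, f(V) 0.25, power at least 0.80. It gives 113 patients; 15 are added for attrition, "totalling 128 patients in total (64 CRT + TAU and 64 SAT + TAU". The abstract divides the same 128 into 64 AN and 64 OCD patients.
- **Analyses.** "The data for the primary AN and OCD outcome indices are analysed using linear mixed models (LMM) with the baseline value as a covariate". The model for CRT's overall efficacy is then listed term by term: a random intercept, condition, time contrasts and condition-by-time interactions. Diagnosis is not among the terms and no common metric for the outcome is stated. Standardisation appears once, for other variables: "Potential continuous moderator variables are standardized". Earlier in the section, closing the paragraph on baseline comparisons, is "Additional exploratory analyses are conducted separately for AN and OCD".

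**The concern.** The sample-size section implies one analysis of all 128 patients with diagnosis as a between-subject factor. The Analyses section lists a model in which diagnosis does not appear and whose response is a different instrument in each half of the sample. A reader cannot tell whether the trial has one primary result or two, or in what unit it will be expressed.

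Either reading has a cost. Stacking raw EDE-Q and Y-BOCS scores makes a one-SD improvement count for different numbers of points in the two disorders, so the pooled coefficient mixes units and follows the scale with the larger spread. Separate models avoid that, but the published power then belongs to an analysis that is not the primary one. The primary aim concerns CRT in AN and in OCD, and the Discussion hopes to learn whether CRT acts on a disorder-specific or a shared mechanism. Neither can be read from a model with no disorder term on mixed scales.

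**Working it through.** **1. Reproducing the plan's figure.** Repeated-measures MANOVA, within-between interaction, Pillai's V, with g between-subject cells and m times:
- s = min(g−1, m−1)
- df1 = (g−1)(m−1)
- df2 = s(N − g − (m−1) + s)
- λ = N·s·f(V)²

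With g = 4 (2 disorders × 2 conditions), m = 3, f(V) = 0.25 and alpha 0.05: s = 2, df1 = 6. At N = 113, df2 = 2(113 − 4 − 2 + 2) = 218 and λ = 113 × 2 × 0.0625 = 14.125, giving power 0.803. At N = 112 power is 0.799. So 113 is reproduced. At the same alpha, two cells with three times need 158, and four cells with four times need 87. The stated figure therefore has both disorders in one model.

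**2. If raw scores are pooled.** Assume equal numbers per disorder, EDE-Q SD set to 1 and Y-BOCS SD equal to r. The ratio r is an assumption, shown from 3 to 8. With standardised effects d_AN and d_OCD:
- pooled raw effect = (d_AN + r·d_OCD)/2
- pooled SD = √((1 + r²)/2)
- AN share of the coefficient at equal standardised effects = 1/(1 + r)

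Power is from a two-sided two-sample t-test with 64 per arm and alpha 0.05. Entries are pooled d / power.

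| r | AN share | 0.5 SD in both | 0.5 SD in AN only | 0.5 SD in OCD only |
|---|---|---|---|---|
| 1 (same as standardised) | 50% | 0.500 / 0.80 | 0.250 / 0.29 | 0.250 / 0.29 |
| 3 | 25% | 0.447 / 0.71 | 0.112 / 0.10 | 0.335 / 0.47 |
| 5 | 17% | 0.416 / 0.65 | 0.069 / 0.07 | 0.347 / 0.49 |
| 8 | 11% | 0.395 / 0.60 | 0.044 / 0.06 | 0.351 / 0.50 |

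Example, r = 5, AN only: raw effect 0.5/2 = 0.25; pooled SD √(26/2) = 3.606; d = 0.25/3.606 = 0.069. This isolates scale: it has no baseline covariate or repeated measures and ignores the difference in mean level between the scales.

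**3. Check with a baseline covariate.** A simulation used 4,000 replicates, 32 patients per arm per disorder, one follow-up, no disorder term and a baseline–follow-up correlation of 0.5. Assumed EDE-Q/Y-BOCS SDs were 1.2/6.0 or 1.5/5.0.
- Raw scores, d = 0.7 in AN only: power 0.09 to 0.14. The same effect in OCD only: 0.83 to 0.85.
- Scores standardised within disorder: 0.58 to 0.59 whichever disorder carries the effect.
- No effect in either disorder, raw scores: rejection rate about 0.05.

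**4. If one model per scale is meant.** g = 2, m = 3, N = 64, f(V) = 0.25: s = 1, df1 = 2, df2 = 64 − 2 − 2 + 1 = 61, λ = 64 × 0.0625 = 4, power 0.40. Power of 0.80 at this f(V) needs 158 patients in each disorder.

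**The case against.** The strongest reply is that the article never says the two scores are stacked. Indices and models are both plural, and research question 1 and Table 1 treat the outcomes as disease-specific, so one model per scale is a natural reading. The sentence "Additional exploratory analyses are conducted separately for AN and OCD" closes the paragraph on baseline differences and may concern only those. The words about general efficacy lead into the moderator paragraph and may mean the overall effect as opposed to effect modification. The sample-size calculation has three measurements in a MANOVA, while the mixed models run to T3, so it cannot settle how the response is built. And a condensed article may leave outcome scaling to a fuller document.

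Most of this stands: pooling is an inference. It does not remove the problem, because under one model per scale the published sample size no longer describes the primary analysis (step 4). Nor is it only detail left elsewhere: the article itself lists the model terms, and they do not match the design it was sized for.

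A reader might go further and infer that the trial's main result is bound to be essentially an OCD result. The documents do not support that. It needs raw stacking and a large SD ratio, and neither is stated; at a ratio of 3, AN still supplies a quarter of the coefficient. Nor does the article specify a single residual variance, since it is silent on residual structure.

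**Conclusion.** The point holds as a contradiction between Outcome measures, Power and sample-size calculation, and Analyses. The arithmetic behind 113 is correct for a four-cell model, but that is not the model listed. What follows depends on the reading:

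- **Raw pooling:** a coefficient without a unit, dominated by the larger-SD scale. The direction favours OCD wherever the Y-BOCS SD exceeds the EDE-Q SD; the size rests entirely on the assumed ratio. Even standardised, an AN-only 0.5 SD effect has power of only 0.29, so part of the weakness comes from averaging over a disorder with no effect. The fault is in what the estimate represents and in power, not in false positives.
- **One model per scale:** no scale problem, but power of about 0.40 per disorder instead of 0.80. This assumes all 64 patients are analysed and keeps f(V) at 0.25, which need not be the same clinical effect in a two-cell as in a four-cell design.

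The text should be reconciled whichever was intended. This is a should-fix point, held with medium confidence because pooling is inferred and no SDs are given.

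**What to change.** Choose one of two routes and say so in Analyses.

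1. **One pooled primary model.** State that each patient's primary score at every visit is standardised within disorder, by that disorder's baseline mean and a stated SD. Include disorder, disorder × time and disorder × condition × time terms. Report the EDE-Q and Y-BOCS effects in raw points beside the pooled effect. Choose the SD with care: OCD entry is restricted ("a Yale-Brown Obsessive-Compulsive Severity Scale score ≥16 is required") and no EDE-Q floor is stated, so the OCD baseline SD may be shrunk, which would enlarge OCD changes in SD units.
2. **Two primary models.** Declare one for EDE-Q in AN and one for Y-BOCS in OCD, make clear that these separate outcome analyses are not exploratory, and restate power per disorder in Power and sample-size calculation.

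The first route costs one derived variable and some wording, and gives a pooled effect in SD units, which clinicians find less familiar. The second keeps clinical units, but the stated power becomes less favourable. Neither needs new data collection.

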### Design

Figure 1 provides an overview of the study design. In a randomized controlled multicentre trial, we compare two treatment arms, i.e. CRT and, in the control condition, Specialized Attention Therapy (SAT), both delivered in 10 twice weekly sessions as an adjunct to TAU for AN and OCD. Patients are assessed at baseline (T0), directly following CRT or SAT completion and prior to symptom based TAU (T1), at 6 months after T0; (T2), and at 12 months after T0 (T3). All patients receive both oral and written information and are enrolled after they have provided written informed consent.

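### The baseline covariate in the primary mixed model drops out of every condition-by-time contrast, so the stated adjustment leaves a change-score comparison and gains no precision

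*Protocol article*

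**What the plan says.** The Analyses section of the protocol article specifies one model for the primary outcomes (EDE-Q for AN, Y-BOCS for OCD). The data "are analysed using linear mixed models (LMM) with the baseline value as a covariate". The models "include a random term for the intercept" and have "fixed terms for condition, time contrasts (T0–T1, T0–T2, T0–T3, T1–T2, T1–T3), and the interactions between condition and time contrasts". No baseline-by-time term is listed. For the moderator models the same section says that the same five contrasts are built by dummy coding.

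Under Design, T0 is baseline, T1 follows CRT or SAT, and the later assessments are "at 6 months after T0; (T2), and at 12 months after T0 (T3"). The sample size rests on a different analysis: "two-tailed MANOVAs, repeated measures and four within-between interactions" with "three measurements (baseline, and 2, and 6 months after baseline").

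**The concern.** The model uses the baseline score twice. Contrasts that run from T0 can be fixed terms only if T0 is a level of time with its own outcome row, so the T0 score is a response. The same score is also a covariate.

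The treatment effect is read from the interactions of condition with the time contrasts, and these compare a patient with himself or herself. A covariate that takes one value per patient, with one slope for all visits, cannot affect such a comparison. For T0–T1, T0–T2 and T0–T3 this happens because T0 is an outcome row. For T1–T2 and T1–T3 it happens whether or not T0 is a row.

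The plan would therefore report a baseline-adjusted analysis while testing unadjusted change. Two things are at stake: the precision that the baseline measurement could have bought, and protection against chance baseline differences, which enter a change score through regression to the mean. Naming one contrast as the only primary test would not cure this, because that contrast would still be unadjusted.

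**Working it through.** **1. The plan's own sample size.** The inputs come from Power and sample-size calculation: "with alpha = 0.05, a sample size of 113 patients is needed" for "power of at least 0.80 to detect an effect size f(V) of 0.25". Take a repeated-measures MANOVA interaction with k = 4 cells (two disorders by two conditions) and m = 3 measurements:

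- s = min(k−1, m−1) = 2, and df1 = 3 × 2 = 6
- df2 = s(N − k − (m−1) + s) = 2(113 − 4 − 2 + 2) = 218
- λ = f(V)² × N × s = 0.0625 × 113 × 2 = 14.125

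Power is 0.803 at N = 113 and 0.799 at N = 112. The figure of 113 is reproduced. It contains no baseline covariate, so it does not depend on the point made here.

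**2. Algebra of the stated model.** For patient i at visit t = 0, 1, 2, 3, with condition gᵢ:

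yᵢₜ = μₜ + α gᵢ + δₜ gᵢ + β yᵢ₀ + uᵢ + eᵢₜ, with δ₀ = 0.

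Subtracting the T0 row from the T2 row gives

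yᵢ₂ − yᵢ₀ = (μ₂ − μ₀) + δ₂ gᵢ + eᵢ₂ − eᵢ₀.

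The terms β yᵢ₀, uᵢ and α gᵢ all cancel. With complete data, the estimate of δ₂ is the difference between arms in mean change. The covariate affects only the condition main effect and the intercept variance.

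**3. Numerical check.** The model was fitted by REML with and without the covariate, and compared with a model that has outcome rows T1–T3 only and T0 as covariate. There were 300 simulated trials of 128 patients per scenario. The 8.5% dropout is 7/82, the earlier attrition quoted in the article. ρ is the correlation between visits, equal for all pairs in this table, and results are in outcome SD units.

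| ρ | Dropout | Largest change in T0–T2 estimate from adding the covariate | Mean model SE, with / without covariate | Empirical SD, with / without | Empirical SD, T0 as covariate only |
|---|---|---|---|---|---|
| 0.3 | 0% | about 10⁻¹⁴ | 0.2091 / 0.2091 | 0.2186 / 0.2186 | 0.1769 |
| 0.5 | 0% | about 10⁻¹⁴ | 0.1768 / 0.1768 | 0.1829 / 0.1829 | 0.1603 |
| 0.7 | 0% | about 10⁻¹⁴ | 0.1369 / 0.1369 | 0.1422 / 0.1422 | 0.1331 |
| 0.5 | 8.5% | 0.033 | 0.1792 / 0.1805 | 0.1731 / 0.1722 | 0.1486 |
| 0.5 | 25% | 0.054 | 0.1847 / 0.1889 | 0.1826 / 0.1820 | 0.1496 |

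With complete data the estimate also equals the raw difference in mean change to about 10⁻¹⁴. At ρ = 0.3 the SE in single trials differs by up to 0.7%, when the intercept variance is estimated as zero. With dropout the covariate lowers the model SE slightly, but the true spread of the estimate does not fall. A correlation that decays over time gives the same picture.

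**4. Size of the loss.** With equal variances and n per arm:

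- Variance of the change contrast: 2(1−ρ) × 2/n
- Variance of the baseline-adjusted contrast: (1−ρ²) × 2/n
- Ratio: 2(1−ρ)/(1−ρ²) = 2/(1+ρ)
- Equivalent total N: 128 × (1+ρ)/2

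At ρ = 0.5 and n = 64, the SEs are √(1 × 2/64) = 0.177 and √(0.75 × 2/64) = 0.153. Illustrative power for a 0.5 SD difference is Φ(0.5/SE − 1.96):

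| ρ | Variance ratio | Equivalent N of 128 | Power, 64 per arm: change / adjusted | Power, 32 per arm: change / adjusted |
|---|---|---|---|---|
| 0.3 | 1.54 | 83 | 0.667 / 0.843 | 0.394 / 0.554 |
| 0.5 | 1.33 | 96 | 0.807 / 0.904 | 0.516 / 0.637 |
| 0.7 | 1.18 | 109 | 0.955 / 0.977 | 0.733 / 0.800 |

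The 32 per arm is one disorder: 64 patients each with AN and OCD (Abstract), allocated 1:1.

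**5. Chance imbalance.** A baseline difference of D shifts the expected change contrast by (1−ρ)D in the opposite direction. For D = 0.3 SD and ρ = 0.5 this is 0.5 × 0.3 = 0.15 SD. The SE of a chance baseline difference is √(2/32) = 0.25 SD with 32 per arm, so 0.3 SD is 1.2 SE and ordinary. With 64 per arm it is 0.3/0.177 = 1.7 SE and less common.

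**The case against.** The strongest reply is that the article never says in words that T0 is an outcome row. The model also cannot be fitted literally: the five contrasts among four visits have rank 3 (T1–T2, for example, is T0–T2 minus T0–T1). On another reading, each contrast is a change score used as the dependent variable with baseline as covariate. That gives the same treatment estimate as analysis of covariance, and the adjustment would then work. Data layout is also something a full plan could settle.

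This reading does not fit the text. The contrasts are listed as fixed terms that interact with condition, and in the parallel moderator analysis they are dummy-coded, so they are predictors and not responses. The rank problem does not rescue the adjustment: a four-level time factor spans all five contrasts, and the covariate cancels from each. The article itself fixes the covariate, the random term and the interactions, and these conflict as stated.

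Several qualifications do stand:

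- T0 as an outcome row is an inference, although a firm one.
- Exact cancellation needs complete data.
- Change-score test describes the estimate; the SE uses the model's pooled residual variance.
- The planned power never relied on baseline adjustment, so this is a forgone gain and not a shortfall against the 113.
- Type I error is not affected.
- Chance imbalance is already reflected in the change-score SE on average, so it should not be counted as a second, additive loss.
- The article describes the analyses separate by disorder as additional and exploratory, which limits the weight of the 32-per-arm figures.

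**Conclusion.** The concern holds. As written, the baseline covariate does nothing for any condition-by-time test: exactly so with complete data, and in practice so with dropout. The comparison remains valid under randomisation, but calling it baseline-adjusted would be wrong.

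The cost is a variance 18% to 54% larger than under real adjustment for ρ from 0.7 down to 0.3. For an illustrative 0.5 SD effect with 64 per arm, power is lower by 0.02 (ρ = 0.7), 0.10 (ρ = 0.5) or 0.18 (ρ = 0.3). Neither ρ nor the 0.5 SD effect is given in the article; both are assumptions, as is equal variance across visits. This should be corrected, but it does not undermine the trial.

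**What to change.** Use the T0 score once, in one of two ways:

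- **T0 as covariate only.** Model T1, T2 and T3 as outcomes, with condition, visit, condition by visit, baseline and preferably baseline by visit. Test the condition difference at the chosen visit.
- **T0 as outcome only.** Keep all four visits as outcomes, drop the baseline covariate and constrain both arms to a common T0 mean.

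In either case, state the effect as the baseline-adjusted CRT minus SAT difference at that visit, and say explicitly which visits are outcome rows. The cost is a change to the analysis wording. No new data or patients are needed, and the sample size stands.
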